## Abstract

**Background:**

Attention deficit hyperactivity disorder (ADHD) is one of the most common neurodevelopmental disorders during childhood; however, the diagnosis procedure remains challenging, as it is nonstandardized, multiparametric, and highly dependent on subjective evaluation of the perceived behavior.

**Objective:**

To address the challenges of existing procedures for ADHD diagnosis, the ADHD360 project aims to develop a platform for (1) early detection of ADHD by assessing the user’s likelihood of having ADHD characteristics and (2) providing complementary training for ADHD management.

**Methods:**

A 2-phase nonrandomized controlled pilot study was designed to evaluate the ADHD360 platform, including ADHD and non-ADHD participants aged 7 to 16 years. At the first stage, an initial neuropsychological evaluation along with an interaction with the serious game developed (“Pizza on Time”) for approximately 30-45 minutes is performed. Subsequently, a 2-week behavior monitoring of the participants through the mADHD360 app is planned after a telephone conversation between the participants’ parents and the psychologist, where the existence of any behaviors characteristic of ADHD that affect daily functioning is assessed. Once behavior monitoring is complete, the research team invites the participants to the second stage, where they play the game for a mean duration of 10 weeks (2 times per week). Once the serious game is finished, a second round of behavior monitoring is performed following the same procedures as the initial one. During the study, gameplay data were collected and preprocessed. The protocol of the pilot trials was initially designed for in-person participation, but after the COVID-19 outbreak, it was adjusted for remote participation. State-of-the-art machine learning (ML) algorithms were used to analyze labeled gameplay data aiming to detect discriminative gameplay patterns among the 2 groups (ADHD and non-ADHD) and estimate a player’s likelihood of having ADHD characteristics. A schema including a train-test splitting with a 75:25 split ratio, k-fold cross-validation with k=3, an ML pipeline, and data evaluation were designed.

**Results:**

A total of 43 participants were recruited for this study, where 18 were diagnosed with ADHD and the remaining 25 were controls. Initial neuropsychological assessment confirmed that the participants in the ADHD group showed a deviation from the participants without ADHD characteristics. A preliminary analysis of collected data consisting of 30 gameplay sessions showed that the trained ML models achieve high performance (ie, accuracy up to 0.85) in correctly predicting the users’ labels (ADHD or non-ADHD) from their gameplay session on the ADHD360 platform.

**Conclusions:**

ADHD360 is characterized by its notable capacity to discriminate player gameplay behavior as either ADHD or non-ADHD. Therefore, the ADHD360 platform could be a valuable complementary tool for early ADHD detection.

**Trial Registration:**

ClinicalTrials.gov NCT04362982; https://clinicaltrials.gov/ct2/show/NCT04362982

**International Registered Report Identifier (IRRID):**

RR1-10.2196/40189

## Introduction

### Background and Objectives

Attention deficit hyperactivity disorder (ADHD) is one of the most common neurodevelopmental disorders during childhood [1]. ADHD is commonly diagnosed during childhood and prolongs into adulthood to a variable extent ranging from 5% to 75% [2]. ADHD is characterized by persistent symptoms of inattention and hyperactivity/impulsivity that interfere with or attenuate social, academic, and occupational functioning, as well as the developmental stage. The symptoms are present prior to the age of 12 years, for a period of at least 6 months in 2 or more settings [3].

The diagnosis procedure remains challenging, as it is nonstandardized, multiparametric, and highly dependent on subjective evaluation of the perceived behavior [4,5]. Additionally, the effectiveness of treatment strategies commonly relies on systematic monitoring using pen-and-paper methods [4,6]. Subjectivity bias, difficulty monitoring in different settings, and risk of data loss are inherent obstacles to these methods.

To address the limitations of the existing approaches, ADHD360 focuses on developing an integrated technology solution that includes a serious game for a probabilistic prediction indicating the presence of ADHD in players using machine learning (ML) models and a mobile app for monitoring ADHD behaviors. The platform aims to (1) facilitate early detection of ADHD characteristics and (2) serve as an adjunct intervention for ADHD management. The first goal of the project is to analyze the gameplay behavior of the users with respect to their diagnosis (ie, ADHD or non-ADHD). Thus, discriminative gameplay patterns among the groups (ADHD or non-ADHD) are explored to estimate the users’ likelihood of having ADHD characteristics. The second goal is to investigate the effectiveness of the platform as an intervention for ADHD management.

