#### ML Methodology

State-of-the-art ML algorithms are used to analyze labeled gameplay data. Specifically, we attempt to classify game-generated data based on the user’s known label (ADHD or non-ADHD). All in-game events of a gameplay session are recorded to form a time series that one can use to reconstruct the whole gameplay session. These events correspond to player actions and environmental parameters, such as performing a jump/move, left or right moving action, obstacle collision, and coin collection. Informative feature extraction is performed by splitting players’ time series depending on the game level. Different feature extraction techniques are assumed for each level depending on its type. In the main runner game, several aggregates are calculated by capturing different events during the gameplay (ie, movement of a player or the ability to avoid obstacles). In the mini games, feature extraction is based on the characteristic game mechanics and events of the respective mini game. The final feature vector of each player is produced by concatenating the individual-level feature vectors.

A schema that includes train-test splitting with a 75:25 split ratio, *k*-fold cross-validation (CV) with k=3, an ML pipeline, and data evaluation was designed for experimental purposes. The train-test splitting is used for model specification (eg, feature selection and model tuning), model selection, and training of the final model. Modeling decisions are made on the training set. Thus, the test set is used only to evaluate and report the statistics of the algorithm’s performance. The purpose of 3-fold CV is to fine-tune the hyperparameters of the supervised learning algorithms (classifiers) that we investigate.

For each classifier, an ML pipeline was designed to include the following procedures: (1) removal of features with 0 variance, (2) univariate feature selection according to a statistical criterion (ANOVA *F* value between label and feature), (3) principal component analysis for dimensionality reduction, and (4) classifier training. Therefore, the hyperparameters of all the steps are tuned (eg, the number of components in principal component analysis) in the 3-fold CV process. The *F1* score is used as the optimization criterion in the 3-fold CV, and the best configuration of each method's pipeline is then used on the entire training set (fully trained pipeline).

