Next, the algorithm with the best-performing pipeline in the 3-fold CV is selected as the proposed method. The general performance of our system on unlabeled data is estimated by evaluating the predictive performance of the proposed method that consists of a fully trained pipeline on the test set. The performance of the ML system is also evaluated based on methods other than the proposed one. The following learning algorithms were applied: k-nearest neighbors (kNN) [37], logistic regression (LogReg) [38], support vector machine (SVM) [39], random forest (RF) [40], ridge classifier (RC) [41], passive aggressive classifier (PAC) [42], stochastic gradient descent (SGD) [43], and naïve Bayes (NB) [44]. For each classifier, we tuned its most important parameters using grid-search CV on a sufficient range of parameter values. The objective of the optimization is to maximize the micro-*F1* score across all validation folds. In addition, we report the performance metrics of accuracy, precision, recall, and *F1* scores.

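### The platform is meant to output a likelihood of ADHD, but models are tuned, selected and reported only on yes/no labels, so the likelihood part of the first goal is not evaluated

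*Protocol article*

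**What the plan says.** The aim is worded as a probability in several places. Background and Objectives describes "a serious game for a probabilistic prediction indicating the presence of ADHD in players using machine learning (ML) models" and says of the first goal that "discriminative gameplay patterns among the groups (ADHD or non-ADHD) are explored to estimate the users’ likelihood of having ADHD characteristics". The Methods paragraph of the Abstract repeats the intention to "estimate a player’s likelihood of having ADHD characteristics".

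The analysis is worded as classification. In ML Methodology, "we attempt to classify game-generated data based on the user’s known label (ADHD or non-ADHD"). For tuning, "The *F1* score is used as the optimization criterion in the 3-fold CV". The same section then says that the optimization maximizes the micro-F1 "score across all validation folds". For evaluation, "we report the performance metrics of accuracy, precision, recall" and F1. The pipeline has four steps and ends with training the classifier.

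Under Gameplay Data, the SVM is selected on its validation F1 and on its gap between training and validation scores. Tables 3 and 4 contain label metrics only.

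**The concern.** Accuracy, precision, recall and F1 depend only on which side of a cut-off each child falls. They take the same values whether the children on one side were scored 0.51 or 0.95. If the platform is to give families and professionals a likelihood, someone has to check that the scores rank children properly and that the stated values are close to the truth. Neither check is among the metrics listed. The metric set is stated in full and the results follow it, so this is a mismatch between aim and analysis and not a detail dropped when the protocol was condensed.

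At stake is what the study can support. It can say something about sorting players into two groups. It cannot say whether a reported likelihood is any good, although that is the stated output. The article also foresees training on a larger data set, and the same mismatch would carry over.

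**Working it through.** **1. Reproduce the SVM test row.** Table 4 gives accuracy 0.85, precision 0.75, recall 1.00 and F1 0.85. All 2x2 tables with 7 or 8 children were enumerated. Only one fits: 3 true positives, 1 false positive, 3 true negatives, 0 false negatives.
- Accuracy = (3 + 3)/7 = 0.857
- Precision = 3/(3 + 1) = 0.75
- Recall = 3/3 = 1.00
- F1 = 2×3/(2×3 + 1 + 0) = 0.857

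No table with 8 children fits, since 7/8 = 0.875. Gameplay Data states 8 test participants; that conflict is a separate matter. The exact (Clopper-Pearson) 95% interval for 6/7 is 0.42 to 0.996. Discrimination is therefore tested, but weakly.

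**2. What selection was based on.** In single-label classification each error is a false positive for one class and a false negative for the other, so micro-F1 = number correct / n = accuracy. Table 3 confirms this: F1 equals accuracy for all eight classifiers, in training and in validation. Selection was in effect on label accuracy.

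**3. What label accuracy hides, from Table 3.** Validation accuracies are multiples of 1/21 and recalls are multiples of 1/9, which implies 9 ADHD and 12 non-ADHD children. (The text states a training set of 22.)

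| | Validation accuracy | ADHD correct | Non-ADHD correct |
|---|---|---|---|
| SVM | 0.6667 = 14/21 | 0.6667×9 = 6 of 9 | 14 − 6 = 8 of 12 |
| SGD | 0.6667 = 14/21 | 1.0000×9 = 9 of 9 | 14 − 9 = 5 of 12 |

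The two tie on the criterion while behaving quite differently.

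Logistic regression models a probability directly. In cross-validation it has recall 0 and accuracy 0.5714 = 12/21, which is what results from labelling everyone non-ADHD. In the test set it has recall 1.00 with precision and accuracy 0.42, i.e. 3/7, which is what results from labelling everyone ADHD. Whether its scores put the children in the right order cannot be seen.

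**4. Same labels, different probabilities.** The article gives no predicted probabilities, so the sets below are assumptions. With a 0.5 cut-off, each reproduces the 6-of-7 table from step 1. Brier score = mean of (p − y)²; log loss = −mean of [y ln p + (1 − y) ln(1 − p)].

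| Assumed p: 3 ADHD / 1 false positive / 3 true negatives | Accuracy | Brier score | Log loss |
|---|---|---|---|
| 0.51 / 0.51 / 0.49 | 0.857 | (6×0.49² + 0.51²)/7 = 0.243 | 0.679 |
| 0.95 / 0.95 / 0.05 | 0.857 | (6×0.05² + 0.95²)/7 = 0.131 | 0.472 |
| 0.95 / 0.51 / 0.05 | 0.857 | (6×0.05² + 0.51²)/7 = 0.039 | 0.146 |

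A constant forecast at the implied test prevalence of 3/7 has Brier score (3/7)×(4/7) = 0.245. One reported accuracy thus covers probabilities that barely improve on a constant and probabilities that are very good.

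**5. How precise an added AUC would be.** Hanley-McNeil at an assumed AUC A = 0.75: Q₁ = A/(2 − A) = 0.600 and Q₂ = 2A²/(1 + A) = 0.643. SE² = [A(1 − A) + (n₁ − 1)(Q₁ − A²) + (n₂ − 1)(Q₂ − A²)]/(n₁n₂).
- 3 ADHD v 4 non-ADHD (implied test set): SE = √(0.5036/12) ≈ 0.205
- 12 v 16 (9 + 3 and 12 + 4, all implied children): SE = √(1.8054/192) ≈ 0.097

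The gain comes from evaluating 28 children instead of 7, not from using probabilities, so it does not measure the mismatch.

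**The case against.** The best reply is that the first goal is also worded as analysing gameplay by diagnosis and finding discriminative patterns, that the Abstract concludes only about discrimination, and that the analysis is called preliminary. This stands in part. A reader might infer that the first goal is not tested at all; the documents do not support that, because Tables 3 and 4 do address two-group discrimination. Calling the analysis preliminary does not close the gap, since the likelihood is named as the output and no listed metric examines it.

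A reader might also infer that the chosen SVM cannot give a probability. The documents do not support this either. SVM scores can be converted, for example by sigmoid (Platt) scaling, and the article neither describes nor excludes such a step. It can only be said that none is described. Likewise, no loss function is given for SGD, so nothing follows about its output.

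Two further replies hold. Tuning on log loss in place of F1 is partly a preference and is not required here. Calibration in this sample is also limited by design: the groups were recruited by diagnosis, so agreement with the observed rate reflects the recruitment ratio and not prevalence in a screening population.

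**Conclusion.** The point holds in a limited form. The stated output is a likelihood, the analysis works on labels throughout, and no probability output is described for the selected model. The likelihood part of the first goal is therefore left unevaluated even if the plan is followed exactly. The discrimination part is evaluated, at 6 of 7 with an exact 95% interval of about 0.42 to 1.00.

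The size of the gap cannot be computed from the article, because it gives no predicted probabilities. The Brier range of 0.039 to 0.243 rests on assumed probabilities and a 0.5 cut-off and is illustrative. The counts of 7, 9 and 12 are back-calculated from Tables 3 and 4 and differ from the stated 8 and 22. The label results themselves are not invalidated. This should be corrected, but it is not fatal to a pilot.

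**What to change.** Choose one of two routes.

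1. **Keep the likelihood aim.** State how each model's score becomes a probability; for the SVM, for example, by sigmoid calibration fitted inside the training folds. Report AUC and a Brier score or log loss, with intervals, beside the existing label metrics. Use the held-out test set or nested cross-validation, so that tuning and model selection never touch the data on which performance is reported; cross-validation that is not nested would be optimistic. State that any calibration result is imprecise and applies only to the recruited mix (18/43 = 42% ADHD), not to a screening population.
2. **Restate the aim** as binary classification of ADHD against non-ADHD gameplay, and remove the probability wording.

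The first route is a reanalysis of data in hand and needs no new participants. Its cost is some extra analysis and wide intervals: at an assumed AUC of 0.75, roughly ±1.96×0.205 = ±0.40 on the implied test set, or ±1.96×0.097 = ±0.19 if all implied children could be used. The second route costs only a change of wording.

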### Literature Summary

Discrepancies regarding ADHD prevalence have emerged over time and among studies, leading to mixed conclusions about the possible underdiagnosis or overdiagnosis of the disorder [7]. Multiple factors have been identified to affect the recognition and diagnosis of ADHD including the parental role, school-based factors, intrinsic factors related to children, and the role of health providers [8].

In terms of the medical aspects, the access to health providers [7], limited reimbursement for specialized mental care [9], differences in clinical approaches, scoring cutoff, and factors related to the medical systems across different countries [10] have contributed to the existing difficulties in the diagnosis process. However, the underlying inconsistencies in the definition of ADHD based on different diagnostic manuals make the recognition and diagnosis of ADHD even more challenging [3,11]. Moreover, ADHD diagnosis could be biased due to the underlying subjectivity of the assessment and information interpretation procedures [12], and the lack of standardization [11].

Although diagnostic challenges could be addressed through a detailed history of prenatal conditions, family status and school/academic life [7,13], standardized tools that could enhance the diagnosis accuracy are necessary.

As early detection of ADHD could ameliorate the disorder’s development, diminish its long-term impact [14], improve quality of life [15], and enhance overall functioning and self-esteem [16,17], research efforts were focused on formulating programs [14,18,19], games [20,21], or game-based tools [22,23] for early diagnosis.

For addressing the existing challenges, ADHD360 aims to develop an integrated platform comprising a serious game and a mobile app for monitoring ADHD behaviors in a SMART (Specific, Measurable, Attainable, Realistic, and Timely) way [24,25] as the core elements. The design of the serious game is based on the Diagnostic and Statistical Manual of Mental Disorders, Fifth Edition (DSM-V) [3] as well as neuropsychological tools. The basic principles of DSM-V and common neuropsychological tools can be easily transferred to the game design process via game mechanics implementation focusing on a specific ADHD behavior.

## Methods

### Study Design

A 2-phase nonrandomized controlled pilot study was performed in the context of the ADHD360 project. The protocol of the pilot trials was initially designed for in-person participation, but after the COVID-19 outbreak, it was adjusted to the new conditions imposed by the pandemic, providing remote participation. The procedures for each of these 2 ways of participation are described thoroughly below.

#### In-Person Participation

The first part of the pilot study begins with a first meeting between the involved members of the research team and the parents of each participant at the Laboratory of Medical Physics and Digital Innovation, School of Medicine of Aristotle University of Thessaloniki (iMedPhys). The aim of this first meeting is to thoroughly inform the parents and the children regarding the nature and scope of the project, as well as the exact procedures that take place according to the research protocol. In this context, parents can ask questions, express any concerns regarding the project, and sign the informed consent form. Afterward, the participants are subjected to a brief neuropsychological assessment by an experienced psychologist from the research team. This neuropsychological assessment includes 6 subtests of the Wechsler Intelligence Scale for Children, Fifth Edition (WISC-V), an intelligence test that measures a child’s intellectual ability, and 5 cognitive domains that impact performance [26]. The 6 subtests of WISC-V used here are (1) similarities, (2) vocabulary, (3) block design, (4) figure weights, (5) digit span, and (6) coding. The main aim of this assessment is to obtain a more integrated view of the participants’ general intellectual abilities in several domains such as verbal comprehension, visual-spatial perception, working memory, processing speed, and fluid reasoning. The average time to complete the subtests is approximately 48-50 minutes. If any of the participants have been assessed by this scale during the past 2 years, they are not reassessed by our research team, and the children’s parents are kindly asked to provide the already existing scores of the aforementioned 6 subtests, if possible. Furthermore, the ADHD Rating Scale-IV [27] is a 4-point Likert brief questionnaire completed by the parents regarding the presence and frequency of ADHD symptoms. Inattention and hyperactivity-impulsivity are the 2 subscales integrated into the ADHD Rating Scale-IV. The total raw score of the scale is calculated by summing the scores of the 2 subscales.

Subsequently, the participants interact with the serious game “Pizza on Time” that has been specifically developed for the ADHD360 project for approximately 30-45 minutes at iMedPhys. During this interaction with the serious game, a form is completed regarding the conditions, the duration and the behaviors that will possibly be occurred. Participants interact again with the serious game for 30-45 minutes at iMedPhys, continuing from the level at which they stopped at the previous visit to complete all the levels of the first setting (the urban setting).

After the aforementioned procedures, there is a telephone conversation between the participants’ parents and the psychologist who conducted the neuropsychological evaluation to discuss if there are any behaviors characteristic of ADHD that affect the daily functioning of the participants. Once the psychologist has reached a consensus with the parents that there are certain behaviors that could be observed, the behaviors are introduced into the participant's account in the mADHD360 app. Instructions regarding the installation and use of the mobile app are provided by the research team through email. The mADHD360 app can be used on a smartphone or tablet. An observation plan is scheduled, including at least 2-4 times per week of behavioral monitoring regarding the frequency or the duration of these behaviors during the time they usually spend with the participant. Each round of behavior monitoring has a duration of 12 minutes. The duration of this phase is determined to be 2 weeks. During the behavior monitoring phase, the participants do not interact with the serious game.

Once behavior monitoring is complete, the research team instructs the participants to continue playing the game using the second (jungle) and third (space) settings on the premises of iMedPhys. The mean duration of this part is 10 weeks with a frequency of at least 2 times a week, depending on the participants’ availability. In this second part of the pilot testing phase, the goal is to exploit the serious game as an intervention to improve certain ADHD symptoms.

Next, a second round of behavior monitoring is performed following the same procedures as the previous one. Furthermore, a neuropsychological assessment is conducted following the same procedures as those during the first evaluation in the beginning of their participation.

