### Recruitment of Participants

We initially considered recruiting at least 20 participants (10 ADHD and 10 non-ADHD) in our pilot trials. We estimated the sample size for the definite study by performing power analysis using GPower software (version 3.1, Universität Düsseldorf). We conducted a paired *t* test analysis using a power of 0.8, a significance level of 0.05, and an effect size equal to 0.2. The total sample size was estimated to be 199 participants. As proposed by Billingham et al [28], the sample size in pilot trials does not need calculation but needs justification. Thus, recruiting a small number of participants seems sufficient according to the suggestions of Stallard [29] and is similar to what was proposed by Julious [30].

The ADHD group is mainly composed of patients from the Community Center for Mental Health of Children and Adolescents at the General Hospital of Thessaloniki “G. Papanikolaou,” which supports the implementation of pilot trials. Furthermore, dissemination activities such as social media posts, mass media interviews, information events open to the public, and project presentations at conferences and workshops are considered essential to recruit participants for pilot trials.

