## Results

### Demographics

In total, 43 participants were recruited with a mean age of 11.82 (SD 2.81) years. Among these, 28 (65%) were male and 15 (35%) were female. Of the 43 participants, 18 (42%) were diagnosed with ADHD and 25 (58%) participants were considered controls (non-ADHD). Approximately 30 participants (70%) completed the first part of the pilot phase remotely.

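### The effectiveness goal cannot be answered: no ADHD child goes without the game, so for this goal the 'controlled' pilot is an uncontrolled before-after comparison

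*Protocol article*

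**What the plan says.** All references are to the Protocol article.

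- **Goal.** Background and Objectives: "The second goal is to investigate the effectiveness of the platform as an intervention for ADHD management". In-Person Participation, on the second part of the study: "In this second part of the pilot testing phase, the goal is to exploit the serious game as an intervention to improve certain ADHD symptoms".
- **Design label.** Study Design: "A 2-phase nonrandomized controlled pilot study was performed in the context of the ADHD360 project". The Methods paragraph of the abstract uses the same label.
- **Who the controls are.** Demographics: "18 (42%) were diagnosed with ADHD and 25 (58%) participants were considered controls (non-ADHD". Recruitment of Participants had planned at least 10 children with ADHD and 10 without.
- **Who plays.** In-Person Participation: "the research team instructs the participants to continue playing the game using the second (jungle) and third (space) settings". The abstract: "the research team invites the participants to the second stage, where they play the game for a mean duration of 10 weeks". Neither sentence separates the two groups. Remote Participation changes only where the game is played.
- **What is measured afterwards.** In-Person Participation: "a second round of behavior monitoring is performed following the same procedures as the previous one". The neuropsychological assessment is also repeated by the same procedures as at the start.
- **Size of the later study.** Recruitment of Participants: "We conducted a paired *t* test analysis using a power of 0.8, a significance level of 0.05, and an effect size equal to 0.2". The result is 199 participants.

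**The concern.** A claim that the game improves ADHD symptoms needs an estimate of what would have happened to similar ADHD children without it. The article describes no ADHD group on a waiting list, in usual care, on a sham game or with a delayed start. The word 'controlled' may lead a reader to think that such a comparison exists. It does exist for the detection goal, where ADHD and non-ADHD gameplay are contrasted, but not for the intervention goal.

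If the plan is followed exactly, the intervention result is a change over 10 weeks or more in children who all play. Maturation, practice on repeated tests, school or lockdown circumstances, and parental expectation would all be part of that change. Parents are told the procedures at the first meeting, so those who complete the rating scale and record behaviours know that the child is playing. A definitive study sized on the same paired change would inherit the problem.

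**Working it through.** **1. Which comparison is left for the second goal?**

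| Element | What the article describes | Does it supply an ADHD comparator? |
|---|---|---|
| Control group | Children without ADHD | No |
| 10-week play phase | Written for all participants, in person or remote | No ADHD child is left out |
| 2-week monitoring before that phase | No play; behaviours counted at least 2-4 times a week | No: a short series that every participant has, taken after the urban-setting sessions |
| After the play phase | Same monitoring and assessment again | No: gives before versus after |

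Only the within-child before-after contrast remains.

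**2. Could the non-ADHD group stand in?** Inputs from Neuropsychological Data and Table 2, ADHD Rating Scale-IV total: ADHD 33.80 (SD 9.94, n = 10); non-ADHD 18.60 (SD 10.62, n = 20).

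- Difference: 33.80 − 18.60 = 15.2 points.
- Pooled SD: √[(9 × 9.94² + 19 × 10.62²)/28] = √(3032.1/28) = 10.41.
- Standardized difference: 15.2/10.41 = 1.46.

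Groups that start about 1.5 SD apart, and are defined by the condition under treatment, cannot be assumed to change alike. This holds whether or not the non-ADHD children also play for the 10 weeks. If they play, they are not a no-game group. If they do not, they are still not ADHD children without the game.

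**3. What does the 199 size?** Inputs from Recruitment of Participants: paired t test, power 0.8, significance level 0.05, effect size 0.2. Sidedness is not stated.

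- Normal approximation, two-sided: [(1.960 + 0.842)/0.2]² = 196.2, so 197.
- Exact noncentral t, two-sided: 199, with power 0.802. This is the stated figure.
- Exact noncentral t, one-sided: 156. This is not the stated figure.

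The 199 is therefore a two-sided test that the mean within-child change is zero. It contains no control term, so its power applies to a change from any cause. As an illustration, suppose the game has no effect but scores shift by 0.1, 0.2 or 0.3 SD of the change score (assumed values, not in the article). The test with 199 children would then be significant in 29%, 80% or 99% of studies.

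**4. How different is a controlled question?** Assume the same standardized effect of 0.2, now as a difference in change between two equal arms of ADHD children. The normal approximation is 2 × (1.960 + 0.842)²/0.2² = 392.4, so 393 per arm; the exact t calculation gives 394. That is 786 to 788 in total. With 199 children split equally, power would be about 29%. Carrying 0.2 over to a between-arm effect is an assumption. The figures show only that 199 does not answer the controlled question.

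**The case against.** The best defence is that this is a nonrandomized pilot. The article separates it from a later definitive study, reports no intervention result, and concludes only about detection. The abstract's Objective speaks of complementary training and contains no effectiveness wording. All of that stands: a pilot may describe feasibility, adherence and before-after change. It does not remove the stated goal, which is effectiveness and is nowhere limited to feasibility. The justification offered for a small pilot concerns its size, not whether a change can be attributed to the game. The Discussion does not list the missing comparator among the limitations.

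Several stronger readings are tempting, and the article does not support them:

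- *Non-ADHD children certainly play the 10-week phase.* The text refers to participants throughout and never says this expressly. The conclusion does not depend on it.
- *Nothing is measured in a period without play.* Two game-free weeks of behaviour counts are scheduled. They give a short trend before the intervention, not a comparator for about 10 weeks.
- *Every outcome is parent-rated.* The repeated assessment includes six WISC-V subtests given by a psychologist. This limits the expectation argument to the rating scale and the parents' behaviour records; the subtests still have no ADHD comparator.
- *Regression to the mean is built in.* Behaviours are agreed before the baseline counts begin, and ADHD children enter on an existing diagnosis with no score threshold. The case is not made.
- *Control children have nothing to monitor.* With a mean rating of 18.60 (SD 10.62), some may well have behaviours to record.
- *A drift of a point or two would equal the planned effect.* The article ties the 0.2 to no outcome and gives no pre-post correlation or drift, so the target cannot be put in scale points.

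**Conclusion.** The point holds for the second goal only. As described, the design cannot show that the platform is effective as an ADHD intervention, because no ADHD child goes without the game and the non-ADHD group is not their counterfactual (15.2 points, about 1.5 pooled SD, apart at baseline). What it can deliver is feasibility, adherence and uncontrolled within-child change. The 199 for the definitive study is arithmetically correct, but for a before-after change.

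The conclusion rests on the described schedule and group definitions, not on any assumed drift. The illustrative drift sizes and the between-arm effect of 0.2 are assumptions and can be set aside without changing it. A reader might also infer that the whole study is uncontrolled or that an effectiveness claim has already been made. Neither follows: the non-ADHD group is a proper comparator for detection, and the article's conclusions are confined to detection.

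**What to change.** 1. **Background and Objectives, and the matching sentence in In-Person Participation:** restate the second goal as feasibility and uncontrolled within-child change in the ADHD group. The abstract's Objective needs no change on this account.
2. **Abstract (Methods) and Study Design:** state that the non-ADHD group is a control for the detection goal only, and that no effectiveness claim will be made from the before-after change.
3. **Recruitment of Participants:** state that the 199 (two-sided paired t test, effect size 0.2) sizes detection of a before-after change, not of an effect of the game against a control.

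These are wording changes and remain possible after data collection. The cost is a less favourable claim.

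A double baseline could be considered for a future cohort, but only if the ADHD Rating Scale-IV is completed at both the start and the end of the game-free monitoring period. The existing first rating will not serve as the starting point, because the urban-setting game sessions come between it and the monitoring. Even then it covers 2 weeks against about 10, and should be presented only as a partial check. It would cost up to two extra completions of a brief parent questionnaire.
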